### 3.5 Data Collection

Interviews will be conducted at the respondent’s home at a location where he/she feels comfortable. In line with global best practice, the study instruments will be developed and reviewed by the study team to ensure that the information collected is relevant to research objectives and policy interests, thereby making the best use of the respondents’ time in the survey.

The survey is expected to last for approximately 45-60 minutes for the head of household interviews and 30 minutes for other adult household members. The survey will be administered in English with translation to Hausa in order to provide respondents with the preferred language option. Households are defined as “a person or group of person, related or unrelated, who usually live together in the same dwelling unit, have common cooking and eating arrangements, and acknowledge one adult member as the head of the household.” The head of household and men or women above 18 years present in the household on the night before the survey are eligible to be interviewed for the survey.

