### 3.4 Selection of Respondents

All adults (over 18 years) will be interviewed in selected households separately with the full survey, excluding the household characteristics, willingness-to-pay, and consumption modules, which will be administered only to the household heads. Women with children will be interviewed on their own health seeking practices as well as those of their children. Adult household members will be asked about individual characteristics (e.g., age, education level), health utilization and expenditures, and health-seeking behaviours. All available eligible adults will be interviewed upon the first visit. In the case where an eligible adult is absent, we will explore the following options: i) Call back to the household to complete the outstanding household members. (ii) Use of mobile phones to interview the eligible adult, if available and allowed by the household respondent.

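### Sections 3.4 and 3.5 conflict on who is interviewed; if the night-before rule governs, spending of usual members who were away can drop out of household out-of-pocket totals

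*Protocol*

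**What the plan says.** Section 3.5 (Data Collection) defines household members as people "who usually live together in the same dwelling unit, have common cooking and eating arrangements". Its next sentence sets eligibility for interview. The head is named without a condition, and beyond the head "men or women above 18 years present in the household on the night before the survey are eligible to be interviewed for the survey".

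Section 3.4 (Selection of Respondents) states a different rule: "All adults (over 18 years) will be interviewed in selected households separately with the full survey". Only the modules reserved for the head are excepted. For absences it says "In the case where an eligible adult is absent, we will explore the following options". The first option is "Call back to the household to complete the outstanding household members" and the second is "Use of mobile phones to interview the eligible adult, if available and allowed by the household respondent".

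The same section collects spending person by person: "Adult household members will be asked about individual characteristics (e.g., age, education level), health utilization and expenditures, and health-seeking behaviours". Reporting for someone else is described only for women answering about their children. Section 3.6 (Questionnaires) assigns the individual inpatient and outpatient expenditure questions to eligible household members, and consumption to the head. Section 2.1 (Primary Objective) defines OOP expenditure as direct outlay by households.

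**The concern.** The protocol uses one criterion, usual residence, to say what a household is. It uses another, presence on one night, to say which of its adults other than the head are asked about health spending. The primary quantity belongs to the household but is assembled from individual interviews, so an adult who is never asked leaves a gap in that household's total.

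The gap need not be random. Anyone in hospital overnight is away by definition, so the presence condition can remove people because they are incurring inpatient costs. Section 3.16 plans weights for nonresponse. A member ruled ineligible is not a nonrespondent, however, and a weight does not restore a missing part of one household's sum. A larger sample would not reduce such a bias, and the missing data cannot be recovered after fieldwork. Section 3.8 provides for three field teams, which could each read the two sections differently.

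**Working it through.** **Step 1. The rules side by side**

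| Adult | Section 3.4 | Section 3.5 |
|---|---|---|
| Head, away the night before | Interviewed | Eligible (no presence condition on the plain reading) |
| Other usual member, present the night before | Interviewed | Eligible |
| Other usual member, away the night before | Interviewed | Not eligible |
| Overnight visitor | Not a household member, so not covered | Eligible only on a loose reading of presence in the household |

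The rules clearly disagree on the third row and arguably on the fourth.

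**Step 2. Do the absence options resolve the third row?** Not clearly. They are triggered when an *eligible* adult is absent, and the only definition of eligibility is in Section 3.5. The call-back wording speaks of outstanding household members, which points the other way. The protocol says only that the options will be explored. Section 3.6 also ties the expenditure questions to eligible members. So if Section 3.5 governs, the third-row adult's spending is not collected by any stated route. If Section 3.4 governs, it is.

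**Step 3. The plan's own figures.** The sample reproduces: 6 LGAs × 17 EAs × 10 households = 1,020. This does not bear on the point. The protocol gives no figure for absent members, visitors or their spending, so there is no stated number to test.

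**Step 4. Illustration under assumptions.** Suppose Section 3.5 governs. Let *a* be the share of usual adults excluded because they were away, and *r* their mean spending relative to adults present, whose mean is set to 1. Both are assumed.

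- True total per usual adult: (1 − a) + a·r
- Total collected with no visitors: 1 − a
- Total collected if an equal share *a* of visitors with mean spending 1 is counted: (1 − a) + a = 1
- Bias: collected ÷ true − 1

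For a = 5%:

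- r = 1: true = 0.95 + 0.05 = 1.00. Omission only: 0.95/1.00 − 1 = −5.0%. With visitors: 1/1.00 − 1 = 0%.
- r = 3: true = 0.95 + 0.15 = 1.10. Omission only: 0.95/1.10 − 1 = −13.6%. With visitors: 1/1.10 − 1 = −9.1%.
- r = 5: true = 0.95 + 0.25 = 1.20. Omission only: 0.95/1.20 − 1 = −20.8%. With visitors: 1/1.20 − 1 = −16.7%.

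Over a wider range (omission only / net of visitors):

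| a | r = 1 | r = 3 | r = 5 |
|---|---|---|---|
| 2% | −2.0% / 0% | −5.8% / −3.8% | −9.3% / −7.4% |
| 5% | −5.0% / 0% | −13.6% / −9.1% | −20.8% / −16.7% |
| 10% | −10.0% / 0% | −25.0% / −16.7% | −35.7% / −28.6% |

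The second figure in each cell is also the bias in mean OOP *per adult* with no visitors, because the mean among those present is 1 and the true mean is (1 − a) + a·r. If absentees spend the average, that mean is unbiased.

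**The case against.** The best defence is that Section 3.4 already has the right rule: all adults are interviewed, and call-backs complete the household's outstanding members. Section 3.5 would then be one careless sentence. This stands in part. A reader might infer from Section 3.5 that absent members are definitely omitted, but that follows only if Section 3.5 governs, and the protocol does not say so. The defect is the unreconciled conflict.

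Four further limits also stand:

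- **The head.** A head who was away or in hospital is not caught by the presence condition.
- **Visitors.** A reader might infer that visitors' spending is planned to be counted. The usual-residence definition, and the references to household members in Sections 3.4 and 3.6, speak against that. Inclusion is possible on the wording but not planned.
- **Catastrophic payments.** It is tempting to say that the numerator loses a member while the denominator, the head's report of consumption, does not. Section 2.2 only names the topic and cites a source. The protocol does not spell out the ratio, so this is a possible consequence and not a demonstrated one.
- **Proxy reports.** That no adult proxy is described does not prove that none will exist. The questionnaire and the instruction manual, neither of which is shown, could provide one, or could capture an inpatient's bill through the relative who paid it.

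What does not stand is treating the matter as detail to be left for later. The eligibility sentence is a stated rule. It decides whose data exist, and no analysis plan can undo it.

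**Conclusion.** The concern holds as a conflict between Sections 3.4 and 3.5 that carries through to the expenditure module in Section 3.6 and can bias the primary quantity. If Section 3.5 governs, usual members other than the head who were away the night before fall outside the interview, and their spending is missing from household OOP.

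The likely direction is downward if absent members spend more than average. Any visitors admitted by the wording would offset part of this, and all of it in the case where absentees spend the average and are replaced one for one by average-spending visitors.

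The size is unknown from the documents. The figures of about 14–21%, and about 9–17% net of visitors, rest on three assumptions: Section 3.5 governs, 5% of adults are excluded, and they spend 3 to 5 times the mean of those present. They show that the effect could matter and are not estimates of it.

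**What to change.** In Section 3.5, replace the night-before condition with a single usual-member rule: every usual household member of interview age is eligible whether or not present the night before, and visitors who are not usual members are excluded. State that this rule governs both the roster and the expenditure module, and align Sections 3.4 and 3.6 with it. Members who were away then come under the existing call-back and phone options with no new procedure.

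For members still not reached, the sponsor may add a report of the household's payments for that member, given by the head or the person who paid. Such records should be flagged, and results shown with and without them. This has to be squared first with individual consent (Section 4, item d, and Section 4.4) and with private interviewing (Section 4.5).

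The core change costs one rewritten sentence, matching edits in the electronic questionnaire and a training note, plus some additional call-backs. Because Section 4 requires approval before any protocol amendment is implemented, it should be made before fieldwork. The optional report brings more recall error and needs an ethics check.

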### 3.6 Questionnaires

There will be one household questionnaire with 11 sections administered to either all eligible members of households or the head of household only. The following modules and their relevant sections include:

- General information (State, LGA, EA name)
- All eligible household members
  - Verbal informed consent
  - Household roster/Individual background information (Name, sex, education, literacy, age, etc…)
  - Health seeking behaviour – inpatient and outpatient services
  - Individual expenditures on health – by inpatient and outpatient services
  - Access to health insurance
- Head of household only
  - Perceived quality of healthcare services
  - Willingness to pay for contributory health scheme
  - Household characteristics
  - Household consumption

Modules will be based on previously used questions from the NDHS and HNLSS and additional questions relevant to the context of the study as appropriate, . The questionnaire will be reviewed and finalized in coordination with the relevant stakeholders; designed and administered using an android application on mobile phones or tablets via an electronic platform; and synchronized with a web-based Survey CTO platform.

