### 2.1 Primary Objective

The overall objective of the study is to estimate the current levels of financial protection on health and out of pocket (OOP) expenditure which is defined as any direct outlay by households, including gratuities and in-kind payments, to health practitioners and suppliers of pharmaceuticals, therapeutic appliances, and other goods and services whose primary intent is to contribute to the restoration or enhancement of the health status of individuals or population groups^[[3]](#footnote-3)^.

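### Out-of-pocket spending is defined to include medicines, appliances and other health goods, but no listed questionnaire section is shown to collect purchases made without a visit

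*Protocol*

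**What the plan says.** Section 2.1 (Primary Objective) sets the quantity to be estimated. OOP is "any direct outlay by households, including gratuities and in-kind payments", paid "to health practitioners and suppliers of pharmaceuticals, therapeutic appliances, and other goods and services whose primary intent is to contribute to the restoration or enhancement", where what is restored or enhanced is health. Suppliers of goods are named alongside practitioners, so a purchase from a supplier counts whether or not a consultation went with it.

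Section 3.6 (Questionnaires) outlines the instrument. Two sections put to all eligible members bear on this point: "Health seeking behaviour – inpatient and outpatient services" and "Individual expenditures on health – by inpatient and outpatient services". The other sections for all members are consent, the roster with individual background, and access to insurance. The household head alone answers on perceived quality, willingness to pay, household characteristics and "Household consumption". The content of the consumption section is not described.

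The same section says that the questions will draw on two earlier national surveys plus additional items, and that the questionnaire is still to be reviewed and finalised. Catastrophic payments are a secondary objective (Section 2.2), and OOP estimates go into the State Health Account (Section 5).

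**The concern.** The definition and the measurement structure do not have the same width. The definition follows the payee and the purpose of the payment. The expenditure section follows the type of service, inpatient or outpatient. Medicines bought over the counter, an appliance, or a preventive product bought without a consultation fall inside the definition but have no evident place in that section.

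The primary estimate, the catastrophic headcount built on it and the figure passed to the State Health Account are all at stake. A coverage gap of this kind works in one direction, and a larger sample does not reduce it. Nor can an analysis plan repair it, because payments that were never asked about cannot be recovered after fieldwork. Section 6 names recall, seasonality and generalisability as limitations, but not coverage.

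**Working it through.** The protocol states no OOP level, catastrophic rate, threshold or precision, so there is no figure of its own to reproduce. The check is a comparison of text, followed by the arithmetic of the bias.

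**Step 1: definition against listed sections.**

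| Component of OOP in Section 2.1 | Named place in Section 3.6 |
| --- | --- |
| Practitioners, during an inpatient or outpatient visit | Individual expenditure section |
| Medicines and appliances supplied as part of a visit | Possibly within the same section; not stated |
| Medicines, appliances and other health goods bought without a visit | None named |
| Gratuities and in-kind payments | Not mentioned |

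**Step 2: is the list complete?** Section 3.6 says "There will be one household questionnaire with 11 sections". The bullets give 1 (general) + 5 (all members) + 4 (head only) = 10. One section is unaccounted for, unless the roster and the individual background count as two. The outline therefore cannot prove that these purchases are left out, and it does not show that they are covered.

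**Step 3: size of the bias if they are not collected.** Let s be the share of true OOP paid outside inpatient and outpatient care. The protocol does not give s; the values below are assumed.

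- Recorded OOP = (1 − s) × true OOP.
- With an assumed catastrophic threshold of 10% of consumption and a complete denominator, a household is flagged only if its true share exceeds 0.10/(1 − s).
- If the same goods are also missing from consumption, the true share needed is 0.10/(1 − s + 0.10s).

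| s (assumed) | Recorded OOP as share of truth | True share needed, denominator complete | True share needed, goods also missing from denominator |
| --- | --- | --- | --- |
| 0 | 100% | 10.0% | 10.0% |
| 0.10 | 90% | 0.10/0.90 = 11.1% | 0.10/0.91 = 11.0% |
| 0.30 | 70% | 0.10/0.70 = 14.3% | 0.10/0.73 = 13.7% |
| 0.50 | 50% | 0.10/0.50 = 20.0% | 0.10/0.55 = 18.2% |

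**Step 4: illustration for the headcount.** Assume a lognormal OOP budget share with mean 8% and coefficient of variation 1.5, the 10% threshold, a complete denominator and the same s in every household. None of these inputs is in the protocol. Then σ² = ln(1 + 1.5²) = 1.179, σ = 1.086 and μ = ln(0.08) − σ²/2 = −3.115. The headcount is P(share > 0.10/(1 − s)): 22.7% at s = 0, 19.9% at s = 0.1, 17.0% at s = 0.2 and 11.1% at s = 0.4. This shows that the headcount can be sensitive to the omission. It is not an estimate for Kaduna State.

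**The case against.** The strongest reply is that a section title in an outline is being read as a measurement rule. A reader might infer that the survey records spending only within visits and that OOP will therefore be underestimated. The protocol does not support that reading:

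- The expenditure line contains no exclusion, and outpatient is not defined, so a drug-shop purchase might be coded there.
- Goods tied to a visit may be itemised within it.
- The consumption module may include health goods, and the list is one short of the stated number of sections.
- Sections 3.1 and 3.4 (Selection of Respondents) describe the health spending to be asked about in broader terms, without the two-way split.
- The questionnaire is not final. Section 3.5 foresees a review against the research objectives, and Section 3.7 a pre-test that asks whether the questions are sufficient.

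All of this stands against a claim of certain underestimation. It does not close the gap. The broader wording in Sections 3.1 and 3.4 names no place for these purchases. If outpatient is meant to include them, nothing says so, and enumerators may classify them differently. The consumption module goes to the head only, and nothing says that any of it enters OOP. Neither the review nor the pre-test is described as checking coverage against the Section 2.1 definition.

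A reader might also infer that the bias would differ by wealth and so distort the comparisons across wealth quartiles planned in Section 3.16. That is possible if s varies with wealth, but nothing in the protocol shows that it does, or in which direction.

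**Conclusion.** The mismatch between the primary definition and the listed expenditure structure is real; the bias is conditional on it. If the questionnaire is built on the structure in Section 3.6 and no other section collects purchases made without a visit, OOP is understated by exactly the uncaptured share. The catastrophic headcount can then only be too low or unchanged, as long as a household's OOP does not exceed its consumption. The size cannot be derived from the protocol: it is zero if s is zero, and 10% to 50% of OOP over the assumed range. The headcount figures rest wholly on assumed inputs and show sensitivity only. The point is best treated as a cheap improvement to make before the instrument is finalised, not as proof that the survey will fail its primary objective.

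**What to change.** Before the questionnaire is finalised:

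1. Add a short third block to the individual expenditure section for health outlays not tied to an inpatient or outpatient visit: medicines bought directly, therapeutic appliances, other health goods, and other practitioners. Ask for cash, gratuities and in-kind payments, and give the block its own recall period.
2. Define OOP as the sum of the inpatient, outpatient and non-visit blocks. Instruct enumerators to record each payment once, under the person treated.
3. If the household consumption module is meant to capture these items, a new block may not be needed. The protocol should then state that those items enter OOP and how double counting with the individual section is avoided.

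The cost is a few items in the electronic questionnaire and a few extra minutes on interviews planned at 45–60 minutes for heads and 30 minutes for other adults. Once the 23 days of fieldwork are over, the missing payments cannot be recovered.

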### 3.7 Pre-test

A pre-test of the draft questionnaire will be conducted in a small number of EAs not selected for the main survey to assess its quality. The pre-test will address the following questions:

- Are the questions and responses valid and reliable?
- Are they appropriate? Are they both necessary and sufficient?
- Do the sections of the questionnaire and the questions within sections have a logical flow?
- Are the skip instructions correct?
- Is there evidence of question order effects?

Others issue that will be addressed are: actual time to complete each questionnaire, clarity of information provided and instructions, question wording, and response categories. Problems and potential errors observed during the pre-test will be addressed and resolved by the study team prior to fieldwork.

### 3.8 Recruitment and Training of Enumerators and Supervisors

Enumerators and supervisors will be recruited from an experienced pool of outsourced staff from Kaduna State. Recruited enumerators will be knowledgeable on current population-based survey methodology and practices. Enumerators will satisfy following criteria:

- Minimum of BSc/HND in relevant Disciplines/Subjects
- Experience in population based survey
- Good communication skills
- Familiarity with the study environments
- Ability to speak local language of the study area
- Experience in the use of electronic data collection will be an added advantage.

We will recruit three teams of data collectors and three supervisors. Each team will consist of six enumerators and an assigned supervisor. Enumerators and Supervisors will participate in a four-day training program inclusive of the pilot test. The training content will include, among others: introduction to the survey, review of the questionnaires, use of Computer-Assisted Personal Interview (CAPI) device, logistics arrangements, role definition for supervisors and enumerators, understanding the survey and survey questions, interviewing techniques, ethical considerations and informed consent, data security, household selection process, and review of survey schedule and process.

The training will have the following objectives:

- Understanding data collection techniques through interviews and use of correct language, behaviour, and ethics
- Understanding the questionnaire content and purpose
- Understanding the logistics and timeframe for the survey
- Practicing and gain fluency in interviewing with the final survey questionnaire, electronic data collection and data security, and the quality improvement checklist as a supervision tool
- Gaining skills in supervision, interviewing and good survey techniques

In addition, the trainees will be given the enumeration area sample maps and survey instruction manual containing: procedures and responsibilities for enumerators and supervisors, examples of problems, causes and remedial actions, quality improvement checklist and daily interview form.

